#### b) Fetal loss and morbidity

1. Fetal death and stillbirth

2. Neonatal death (i.e. from birth to 28 days)

3. Post-neonatal death (29 days to 2 years)

4. Individualized birth weight Z score (i.e. birth weight adjust for gestational age, maternal height, maternal weight at booking and ethnic group).

5. Apgar score

6. Cord blood ph

7. Gestational age at birth

8. Intraventricular haemorrhage

9. Neonatal enterocolitis

10. Neonatal convulsions

11. Congenital abnormality

#### c) Maternal morbidity and mortality

1. Maternal mortality

2. Mode of delivery

3. Proteinuria

4. Hypertension in pregnancy

#### d) Early childhood outcomes

1. Behaviour and development at 2 years

2. Disability at 2 years

3. Respiratory symptoms at 2 years

#### e) Health economic data

1. Duration of maternal hospital admission for childbirth

2. Duration of any admission (of baby) to special care

3. Health status at 6 months (EQ5D) [20]

### Sample size

We need to recruit 525 women into each arm of the study. A trial with 500 women in each arm would detect an absolute difference of 9% in smoking cessation rates between the two groups immediately before childbirth with a two-sided significance level of 5% and a power of 93%. We anticipate that up to 5% of women will be lost to follow up and inflate our sample size (of 500) by a factor of 1.05 to allow for this. This size of study would allow us to detect smaller treatment effects with lower power. For example, we would have 80% power to detect an absolute difference in cessation rates of 7%.

A Cochrane review has shown that approximately 10% of women who are still smoking at the time of their first antenatal visit will stop smoking with usual care and a further 6% to 7% will stop as a result of a formal smoking cessation program using intensive behavioural counselling [15]. This means that in our control group (*placebo plus intensive behavioural counselling*) we can expect a smoking cessation rate of around 16%. The most recent Cochrane review of NRT, reports a treatment effect (odds ratio) for transdermal patches of 1.74 95%CI (1.57–1.93) [5]. Consequently, if we were to find NRT as effective in pregnancy as it is generally, we could expect a smoking cessation rate of approximately 25% in our treatment group (*NRT plus intensive behavioural counselling*).

### Inclusion criteria

Eligible women are women between 12 and 24 weeks pregnant, who report smoking at least ten cigarettes daily *before *pregnancy and who *still currently *smoke at least five cigarettes daily. They also must have an exhaled CO reading at least 8 ppm. Women may only enrol into the trial once and may participate in other non-conflicting research projects.

### Exclusion criteria

Women with the following contraindications to the use of NRT will be excluded: severe cardiovascular disease, unstable angina, cardiac arrhythmias, recent cerebrovascular accident or TIA, chronic generalized skin disorders or known sensitivity to nicotine patches, chemical dependence/alcohol addiction problems. Also, women who cannot give informed consent and those with known major fetal anomalies will be excluded. IUGR is not an exclusion criterion.

### Recruitment (see Figure 1)

**Figure 1 F1:**
[figure not shown]
**Flow of trial participants from recruitment to delivery**. Research midwives in each centre are responsible for accurate data entry to internet hosted database, for sending blood samples to appropriate university departments and accurate paper copies of data collection sheets from i) baseline (pre-randomisation) ii) one month follow up and iii) delivery to the Nottingham Trial Co-ordinating Team.

All pregnant women between 12 and 24 weeks into pregnancy who smoke and are interested in stopping smoking are potentially recruits to the study. Brief information about the trial and patient information sheets (PIS) will, therefore, be posted to all women who attend trial site hospitals for ante natal care with their routine antenatal ultrasound scan appointment letters (scans are usually performed at between 12 and 20 weeks gestation). In each trial hospital, a w.t.e. research midwife (RM) working with non-w.t.e. clerical assistant will use a systematic method to identify smokers who are interested in participating from all women attending for ultrasound examinations. During piloting a questionnaire was used for this and a similar instrument could be used in any or all of the 5 trial centres. The final method of identifying eligible patients will be agreed with the Chief Investigator. Research midwives will also agree a method for monitoring the numbers of women identified as potentially eligible to join the trial and the proportion of these that eventually enrol.

### Consent

Women who are interested in participation will be asked to discuss this with the research midwife. The research midwife will ascertain if women are eligible to join the study and have read the PIS at least 24 hours earlier. If they have read the PIS, the research midwife will answer any questions that women have about trial enrolment and seek informed consent to:

i) trial participation

ii) collection of follow up data on materno-fetal outcomes from medical records

iii) participants' registration with the Office for National Statistics

iv) collection of a blood sample for cotinine estimation and DNA extraction & storage

v) collection of saliva samples for cotinine estimation

vi) potential future contact for follow up studies by University of Nottingham based investigators

If women have not read the PIS, but express an interest in the study, they will be given a copy and contacted after 24 hrs to determine whether or not they consent to enter the trial. These women will be contacted after 24 hrs and if they are still interested in enrolling in the study, informed consent will be sought.

Once consent is recorded, baseline data, saliva, blood samples and exhaled CO readings are obtained. Next the research midwife delivers the first session of behavioural support to the participant during which a quit date which is within 2 weeks when they will start using transdermal patches is agreed.

### Registration & randomisation

Immediately after the behavioural support session, the research midwife uses a PIN to log on to the University of Nottingham internet randomisation service and enters the ***mandatory enrolment data ***below, without which randomisation will not be permitted. The participant is automatically allocated a trial number (i.e. unique ID) and a trial treatment pack number which identifies the treatment required and the RM issues the corresponding trial treatment pack.

It is anticipated that around 50% of trial participants will need a home visit for intensive behavioral counseling and subsequent randomization. In this situation, the research midwife (RM) will ensure that all base line data including the ***mandatory enrolment data ***is collected whilst visiting the participant. The RM will return to base and randomization the participant via the internet before posting an appropriate treatment pack to the study participant.

The research midwife then sends letters to the participant's general practitioner and hospital obstetrician to inform them that she is enrolled in the trial. One copy of the consent form is placed in the hospital medical records, another accompanies the letter to the GP and the third is sent to the Trial Office.

### Further behavioural support

The research midwife will give the participant contact details for the local NHS stop smoking service and also pass the participants' details to this service. Participants will receive up to 5 further behavioural support sessions from the NHS stop smoking service according to an agreed format.

### Data handling

RMs will enter the data which they collect on to a secure database hosted by the University of Nottingham via an internet connection and will also make paper copies of data collection to allow audit. Once data collection at any one time point (e.g. baseline or one month) is complete, the research midwife will photocopy the data collection sheet and post a copy to the Trial Office. Infant records within the database will be created from within maternal ones and will automatically be linked to maternal and sibling trial records.

### Biological samples

i) For DNA extraction, 2 × 5 ml EDTA blood samples are required. These can be refrigerated or frozen (if later than 24 hrs elapses between collection and dispatch). If frozen, this needs to be to -20° centigrade. Samples will be dispatched to [name] at the University of Nottingham for long term archiving. Frozen samples require non-glass tubes.

ii) Blood for serum cotinine estimation (5 ml sample minimum) need to be placed in BD Gold top tubes (or equivalent). These need to be frozen as per i) above before transport to the Nottingham Trial Coordination Team prior to dispatch to [name] at the University of Dundee.

iii) Saliva for salivary cotinine estimation is also transported to Dundee after collection.

All frozen samples need to be transported on ice in non-glass containers labelled with:

• Trial number

• Hospital number

• Subject's initials

### Withdrawal from patch treatment

If for any reason, a participant terminates patch treatment, every effort must still be made to collect follow up data.

### Follow-up at one month after agreed quit date

Participants will return to the research midwife (RM) for further supplies of patches. To allow some flexibility this follow up will occur between 3 and 6 weeks after randomisation. The RM will ascertain women's smoking status and those who report not smoking regularly (confirmed by exhaled CO measurement) will be issued with a new trial treatment pack number (obtained by the RM from the online database) and will receive a corresponding treatment pack (containing 4 weeks' patches). A saliva sample to measure cotinine levels on treatment will be taken. The Trial Office will send a postal questionnaire asking about smoking status to women who do not return at one month. One postal and telephone reminder will be used. When women report continued smoking cessation and do not attend for further NRT, the research midwife will contact them to arrange CO validation of this, visiting them at home, if necessary.

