### Treatment group

Pregnant women will receive an eight week course of 15 mg/16 hr NRT transdermal patches. Although many studies have used longer courses, there is no evidence that these are more effective [5]. Patches will be issued in conjunction with individual behavioural support (*Section 10*) which is an effective smoking cessation intervention in pregnancy [7]. Four weeks after their quit dates, women who are not smoking will be issued with a second four week supply of patches.

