### Outcome measures

These relate to smoking, fetal loss, fetal and maternal morbidity and health economic outcomes.

Primary end point: Self-reported, prolonged and total abstinence [19] from smoking or the use of any non-pharmacological nicotine containing substances between a quit date set within two weeks of randomisation and immediately prior to childbirth.

Prolonged abstinence cannot be comprehensively validated, but if participants report prolonged abstinence and are abstinent at ***both ***time points below, they will be considered tohave a positive primary outcome. This is **one **outcome requiring **three **different measures to be achieved.

i) Self reported smoking cessation for at least 24 hours before follow up at one month after quit date, ***validated by ***exhaled CO measurement [cut off 8 ppm [17]].

ii) Self reported smoking cessation for at least 24 hours before hospital admission for childbirth, ***validated by ***exhaled CO measurement [cut off 8 ppm [17]].

Secondary end points:

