#### a) Smoking

1. Self reported, prolonged abstinence [19] from smoking between quit date and one month.

2. Self reported, prolonged abstinence [19] from smoking between quit date and 6 months after delivery.

3. Self reported smoking cessation for previous 7 day period at 6 months after delivery (point prevalence) [19].

4. Self reported, prolonged abstinence [19] from smoking between quit date and 2 years after delivery.

5. Self reported smoking cessation for previous 7 day period at 2 years after delivery (point prevalence) [19].

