##### i) Mandatory enrolment data (i.e. required for randomisation)

The RM will collect the following data from participants immediately after obtaining informed consent. The RM **must **enter the following data items about participants to the online database **before **randomisation is permitted:

*DoB *(valid range equiv to age 14–50)

participant's initials

hospital number

*daily number of cigarettes smoked before pregnancy*[28]

*daily number of cigarettes smoked currently*[28]

*agreed gestational age at time of randomisation *(valid range 12^0^–24^6^) [estimated delivery date will be calculated automatically within database]

time elapsed since last cigarette

exhaled CO reading of at last 8 ppm

*blood sample requested *(for cotinine assay, DNA extraction & storage)

indication that patient has signed consent form

*indication that participant's contact details have been recorded on paper *(see below)

agreed quit date

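### The one-month visit is windowed from randomisation while the measures and re-supply that rely on it run from the quit date, so a visit inside the window can fall 7 to 42 days after quitting

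*Protocol article*

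**What the plan says.** Most of the protocol article ties this visit to the quit date:

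- **Treatment group.** The course is set by "Pregnant women will receive an eight week course of 15 mg/16 hr NRT transdermal patches", and re-supply by "Four weeks after their quit dates, women who are not smoking will be issued with a second four week supply of patches".
- **Outcome measures.** One of the three requirements of the primary outcome is "Self reported smoking cessation for at least 24 hours before follow up at one month after quit date", validated by exhaled CO.
- **Secondary end points, a) Smoking.** The first item is self-reported prolonged abstinence "from smoking between quit date and one month".
- **Data collection, item b).** The form for this visit is also headed by the quit date.

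The section Follow-up at one month after agreed quit date gives the only tolerance, and counts it from a different day: "To allow some flexibility this follow up will occur between 3 and 6 weeks after randomisation".

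The Abstract and Outcome measures place the quit date within two weeks of randomisation. The Interventions section says that patches start on the quit date.

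**The concern.** The visit has two clocks. What it is meant to measure and trigger runs from the quit date; when it may happen runs from randomisation. The two can differ by up to two weeks, which is large against a nominal four.

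Two things are at stake. First, the visit labelled as one month may be held much earlier, so one-month abstinence is recorded after different lengths of follow-up in different women, and the second pack may be released before the four-week condition can be judged. Second, and of less weight, a visit late in the window may come after the first patches have run out, leaving an abstinent woman untreated for some days.

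**Working it through.** **Inputs**

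- Visit window: 3 to 6 weeks after randomisation, which is day 21 to day 42 (Follow-up at one month after agreed quit date).
- q, the days from randomisation to quit date: 0 to 14 (Abstract; Outcome measures). It is taken as not negative because the patches that start on the quit date are issued after randomisation.
- Length of the first pack: not stated. It is inferred from Treatment group as an eight-week course less a second supply of four weeks, so 4 weeks or 28 days.

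**Formulas**

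- Days since quitting at the visit = visit day − q.
- Earliest visit = 21 − q. Latest visit = 42 − q.
- Longest gap in patches with daily use = (42 − q) − 28 = 14 − q.
- Day 28 after quitting falls on randomisation day 28 + q.

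**Results**

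| q (days) | Earliest visit after quitting | Latest visit after quitting | Longest patch gap | Day 28 after quitting, as day after randomisation |
|---|---|---|---|---|
| 0 | 21 | 42 | 14 | 28 |
| 7 | 14 | 35 | 7 | 35 |
| 10 | 11 | 32 | 4 | 38 |
| 14 | 7 | 28 | 0 | 42 |

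Over all women the range is 21 − 14 = 7 days to 42 − 0 = 42 days, against a nominal 28.

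The last column always lies between 21 and 42, so every woman can be seen four weeks after quitting without leaving the window. The window simply does not require it.

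**Would moving the anchor be enough?** If the same 21 to 42 days were counted from the quit date, the earliest visit would be day 21 for everyone. The longest patch gap would become 42 − 28 = 14 days whatever the value of q. The anchor causes the early visits; the six-week upper limit causes the gap. They need separate remedies.

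**Sample size.** The power calculation does not use the timing of this visit. It recomputes to 94% for 16% against 25% with 500 per arm (93% stated) and is unaffected.

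**The case against.** The strongest reply is that the window should not be read alone. The section heading, Treatment group, Outcome measures and the data form all say four weeks or one month from quitting, and the window is offered only as flexibility around that. It contains day 28 for every woman, and its upper limit is what the latest quitter needs (14 + 28 = 42). Giving out a second pack on day 7 would itself breach Treatment group. This stands to the extent that the rules can be obeyed together. It does not remove the point, because no section sets a minimum time since quitting, and the one operational rule a midwife would schedule by is the randomisation window.

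A second reply is that the timing can be recovered: the quit date and the follow-up date are both recorded, and the visit form asks about smoking since the quit date, with further detail on a form not shown. Time since quitting is indeed known for each woman seen. Smoking after an early visit is not. The delivery question on smoking since the quit date settles one-month status for women abstinent throughout, but not for a woman abstinent at an early visit who relapsed later, unless the unseen form dates the relapse.

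A third reply concerns the patch gap. It rests on an inferred pack length, daily use, an early quit date and a late visit, and women return precisely to collect more patches. In addition, "It is anticipated that around 50% of trial participants will need a home visit for intensive behavioral counseling and subsequent randomization", and their packs are posted, so a quit date on the day of randomisation, and with it the full 14 days, is unlikely for them. The gap is therefore only a minor scheduling point.

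A reader might also infer that an early visit cuts the validated abstinence in the primary outcome from a month to a week. The documents do not support that. The component is a 24-hour report with a CO check whenever it is done; an early visit only moves that spot check earlier.

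**Conclusion.** The point holds as an inconsistency in visit timing. A visit within the stated window can fall 7 to 42 days after quitting, and nothing in the article prevents the early end. The 7-day figure is an extreme: it needs the latest quit date and the earliest visit.

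The consequence is modest. For the primary outcome it is limited, since a woman seen early must still report abstinence to delivery and pass the check there. The first smoking secondary outcome and the four-week re-supply condition are more exposed, because both depend on this visit being near four weeks.

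A reader might infer a bias between arms. The documents do not support one: the same window applies to both groups, and participants and midwives are blinded. Nor can a share of affected women be given. The part of the window lying before day 21 after quitting is q/21, from 0% to 67% (14/21), but that counts permitted days, not visits, and the spread of quit dates and visits is unknown.

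The patch gap of up to 14 days assumes a 28-day first pack used daily.

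**What to change.** - **Re-anchor the window.** Count it from the quit date, with a target of four weeks and a lower limit of 21 days after quitting. Accept visits up to 42 days after quitting for CO validation.
- **Visits before day 28.** Record the date and confirm smoking status to day 28 later, by the telephone or postal contact already in use or at delivery.
- **Re-supply.** Book it at or just before day 28. The follow-up section already provides, for women who report cessation but do not attend, that "the research midwife will contact them to arrange CO validation of this, visiting them at home, if necessary". For women seen at home, issue or post the second pack after CO confirmation. It should not simply be carried to the visit, because the pack number comes from the online database and issue depends on confirmed abstinence.

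The cost is small. The timing sentence changes, and the database calculates a due date from the "agreed quit date", which must be entered before randomisation. No extra participants or samples are needed. The downsides are slightly tighter scheduling, a short follow-up contact for some women seen early, and a patch gap that may remain for late attenders.

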### Follow-up immediately before childbirth

When participants are admitted to hospital whilst in established labour *prior to childbirth*, Delivery Suite staff will contact the research midwife who will visit participants to ascertain their self-reported smoking status and use of transdermal patches. Women who report abstinence from smoking in the previous 24 hours will be asked by the research midwife to perform exhaled CO testing and provide a saliva sample for cotinine estimation. The RM will have overall responsibility for data collection and will arrange with Delivery Suite staff for this to be obtained in her/his absence. The RM will telephone those missed whilst in hospital as soon as possible afterwards (within 2 weeks maximum) to collect smoking behaviour data. Where participants report smoking cessation, the research midwife will measure their exhaled CO readings and obtain a saliva sample for cotinine estimation, visiting women at home if necessary.

Further infant, fetal and maternal data will be obtained from medical records (*details below*)

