#### c) Upon admission for childbirth

The following data are recorded by the RM or delivery suite staff:

Date of follow up/exhaled CO reading or saliva sample

Smoked at all in the 24 hrs prior to delivery

Smoked between quit date and delivery

One or both of, *i) exhaled CO reading & ascertainment date ii) saliva sample *(for cotinine)

On how many days have patches been used?

On how many days (if any) have non-trial patches been used?

How many behavioural support sessions with NHS stop smoking services used (telephone & face to face)?

i) These data obtained by RM from ***maternal ***or ***infant medical records before ***discharge. For reasons of data protection some personal infant details are recorded on paper rather than being transmitted over the internet to the trial database:

*maternal *

hypertension (>140/90) on 2 occasions (excluding labour)

miscarriage (between randomisation and 24 weeks)

labour onset (spontaneous, induced, no labour)

mode of delivery (SVD, instrumental, caesarean)

ante natal or post natal maternal hospital admission

*infant*

baby initials

D.O.B

Gender

Baby NHS number

*Prompt for RM to confirm full name and address and contact details of baby and to record these on paper *(see below)

Prompt for RM to make a new record of contact details if these have differed from previous (i.e. maternal) ones

baby hospital number

birth weight

Number of births

if multiple birth, indicate number and birth order

live or stillbirth?

cord ph < 7.0

Apgar <7 at 5 min

*Gestational age at birth *– to be calculated within database from gestation at recruitment

These infant personal details will be recorded on paper only:

baby name

baby address (inc postcode)

ii) These data obtained by research midwife from ***infant medical records after ***discharge:

If live birth? live on leaving hospital

ventilation > 24 hrs

necrotising enterocolitis

neonatal convulsions

admitted to special care

*intraventricular haemorrhage *(4 categories)

*congenital abnormality present (y/n). If y then free text to describe this*.

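### The delivery assessment of the primary endpoint is prompted by admission in established labour, but the endpoint and the data form place it at any admission for childbirth, including births with no labour

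*Protocol article*

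**What the plan says.** The protocol article deals with the timing of the delivery assessment in three places.

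- **Outcome measures.** The primary endpoint runs "between a quit date set within two weeks of randomisation and immediately prior to childbirth". Its delivery component is "Self reported smoking cessation for at least 24 hours before hospital admission for childbirth", validated by exhaled CO with a cut-off of 8 ppm. It is one of three measures that must all be met; the others are reported abstinence throughout and CO-validated abstinence at one month.
- **Follow-up immediately before childbirth.** Delivery Suite staff contact the research midwife "When participants are admitted to hospital whilst in established labour". The midwife "will arrange with Delivery Suite staff for this to be obtained in her/his absence". The only other route is retrospective: "The RM will telephone those missed whilst in hospital as soon as possible afterwards (within 2 weeks maximum"). If a woman contacted in this way reports cessation, "the research midwife will measure their exhaled CO readings and obtain a saliva sample for cotinine estimation, visiting women at home if necessary".
- **Data collection, part c.** The heading is "Upon admission for childbirth", with no labour condition, and the midwife or delivery suite staff record the data. The items include "labour onset (spontaneous, induced, no labour") and caesarean as a mode of delivery.

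**The concern.** The follow-up section is the only place that says who alerts the midwife and when, and its prompt is narrower than the endpoint it serves. A woman who never labours cannot meet it. A woman admitted for induction, or already an antenatal inpatient, is not admitted in established labour. The protocol's own form shows that such births are expected.

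At stake is the objective part of the primary endpoint. A CO reading reflects recent smoking only. If it is taken after the birth, it no longer tests the period before admission. The error can then run either way: a woman abstinent to delivery who has since relapsed can fail, and a woman who smoked up to admission can pass after a spell in hospital without smoking. Under the primary analysis, women who are not reached count as smokers.

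**Working it through.** **1. The passages side by side**

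| Section | What prompts or times the assessment | Births covered on a literal reading |
|---|---|---|
| Outcome measures | Hospital admission for childbirth | All hospital births |
| Data collection, part c | Admission for childbirth; form lists induced and no labour | All hospital births |
| Follow-up immediately before childbirth | Admission in established labour | Not births without labour; not admissions before labour |

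**2. What follows for each group if the follow-up section is applied as written**

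- *No labour.* The prompt never occurs. The one remaining stated route is the telephone call after the birth, within 2 weeks, with CO and saliva after that call.
- *Induced, or already an inpatient.* The woman may be seen before birth once labour is established. The preceding 24 hours may then be partly or wholly hospital time, so the CO reading is a weaker check on the period before admission.
- *Self-report.* This survives a delay, because the questions can refer back to the time before birth. The biochemical check does not.

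**3. The plan's own power figure**

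Inputs from the Sample size section: n = 500 per arm, p1 = 0.16, p2 = 0.25, two-sided 5%, stated power 93%.

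Formula: power = Φ{[(p2 − p1)√n − 1.96·√(2·p̄·(1 − p̄))] / √(p1(1 − p1) + p2(1 − p2))}, where p̄ = 0.205.

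Numerator: 0.09 × 22.36 − 1.96 × 0.571 = 2.012 − 1.119 = 0.893. Denominator: √(0.1344 + 0.1875) = 0.567. Ratio 1.575, so power = 94.2%. The stated 93% is reproduced within rounding and choice of formula: 93% power needs 473 per arm, or 495 with continuity correction.

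**4. Illustration of dilution (m and f are assumed; the document gives neither)**

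Let a share m of women fall outside the trigger, and let a fraction f of the true abstainers among them be counted as smokers, equally in both arms. Both success rates are multiplied by k = 1 − m·f.

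| m | f | k | Rates | Difference | Power, 500 per arm |
|---|---|---|---|---|---|
| 0 | – | 1 | 16.0% v 25.0% | 9.0 points | 94.2% |
| 10% | 25% | 0.975 | 15.6% v 24.4% | 8.8 points | 93.6% |
| 20% | 50% | 0.90 | 14.4% v 22.5% | 8.1 points | 91.1% |
| 30% | 50% | 0.85 | 13.6% v 21.25% | 7.65 points | 89.2% |
| 30% | 100% | 0.70 | 11.2% v 17.5% | 6.3 points | 81.2% |

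The last row is an extreme, since the retrospective route will recover some abstainers and so keep f below 100%. The table covers false failures only.

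**5. The opposite error**

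Assume a smoker starts at 20 ppm with a CO half-life of 4 to 5 hours (neither figure is in the document). The time to reach 8 ppm is half-life × log2(20/8) = half-life × 1.32, or 5.3 to 6.6 hours. On those assumptions, part of a day in hospital without smoking is enough to pass the CO check.

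**The case against.** The strongest reply is that two of the three sections already cover these women. The endpoint definition and the data-collection list both speak of admission for childbirth without a labour condition, and the form expects induced and no-labour births. The midwife has overall responsibility for data collection and arranges cover. The telephone route is for women missed in hospital, and nothing forbids measuring a woman at a booked admission. The article is also condensed, so site instructions may handle booked admissions.

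Much of this stands. A reader might infer that the trial has chosen to measure planned caesareans after the birth. The document does not support that; it shows an inconsistency between sections. The inconsistency is still a fault, because the data list names items and tells nobody to make the call, while the one section that does so states a narrower condition. This is an explicit rule that conflicts with the endpoint, not a detail left to a fuller document.

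Three further inferences are tempting and also go too far.

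- *That a low CO in hospital would confirm almost any smoker.* The endpoint also needs reported abstinence from the quit date and a CO-validated pass at one month. Time in hospital also lowers CO in women tested during labour, so this weakness is not confined to the group outside the trigger.
- *That relapse would fail most late-tested abstainers.* The Background says about two thirds of women who stop in pregnancy restart post-natally, but gives no time frame, so the share relapsing before the late contact is unknown.
- *That the error biases the comparison between arms.* Participants and midwives are blind and both arms follow one procedure. Mode of delivery is a secondary outcome, but nothing in the document points to a treatment effect on it large enough to matter here.

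**Conclusion.** The concern holds as a contradiction between the trigger in the follow-up section and the timing in the Outcome measures and Data collection sections. Followed literally, the trigger leaves births without labour with no CO check before birth, and it may leave induced women and inpatients tested only after time in hospital. What is lost is mainly the timing of the biochemical validation, not the self-report.

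The likely consequence is misclassification similar in both arms. False failures would shrink the 9-point difference; false confirmations run the other way and are limited by the other two components. No net size can be derived. On the assumed values above, power moves from 94.2% to between 93.6% and 89.2% in the moderate cases and to 81.2% in the extreme one.

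A reader might want a head count of women affected. Any such count would rest on assumed shares of no-labour and induced births, and counting every induced woman as missed would overstate it, since many could be seen once in labour. The case for the change rests on the conflicting passages and the low cost of reconciling them, not on a demonstrated loss.

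**What to change.** In Follow-up immediately before childbirth, replace the established-labour condition with: any hospital admission expected to lead to birth (spontaneous labour, induction or planned caesarean) or, for women already inpatients, the point at which delivery is decided. Ask the smoking questions and take the CO reading then, before the birth. Keep the post-birth telephone and home-visit route only for women missed despite this. The Delivery Suite instructions should carry the same wording.

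This changes only when a measurement is taken. The staff and the test stay the same. The small downside is that the midwife must check booking lists for planned admissions.
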